## Abstract

**Background:**

Patients with end-stage renal disease (ESRD) are at high risk of cardiovascular events. Multiple risk factors for atherosclerosis are present in ESRD and may contribute to the increased risk of cardiovascular mortality in this population. In contrast to patients with normal renal function, the benefits of modifying lipid levels on cardiovascular outcomes in patients with ESRD on haemodialysis have yet to be confirmed in large prospective randomised trials. A study to evaluate the Use of Rosuvastatin in subjects On Regular haemodialysis: an Assessment of survival and cardiovascular events (AURORA) will be the first large-scale international trial to assess the effects of statin therapy on cardiovascular morbidity and mortality in ESRD patients on chronic haemodialysis.

**Methods:**

More than 2,750 ESRD patients who have been receiving chronic haemodialysis treatment for at least 3 months have been randomised (1:1), irrespective of baseline lipid levels, to treatment with rosuvastatin 10 mg or placebo. The primary study endpoint is the time to a major cardiovascular event (first occurrence of cardiovascular death, non-fatal myocardial infarction or non-fatal stroke). Secondary endpoints include all-cause mortality, major cardiovascular event-free survival time, time to cardiovascular death, time to non-cardiovascular death, cardiovascular interventions, tolerability of treatment and health economic costs per life-year saved. Study medication will be given until 620 subjects have experienced a major cardiovascular event.

**Conclusion:**

Our hypothesis is that results from AURORA will establish the clinical efficacy and tolerability of rosuvastatin in patients with ESRD receiving chronic haemodialysis and guide the optimal management of this expanding population.

## Background

Patients with end-stage renal disease (ESRD) undergoing haemodialysis have substantially higher cardiovascular disease mortality rates than the general population [1-5]. Accelerated atherosclerosis has been observed in haemodialysis patients [6] and may contribute to this increased cardiovascular event rate. Treatment of ESRD and its cardiovascular consequences places a large burden upon healthcare providers, and the cost and prevalence are expected to increase greatly over the next decade [5]. Therefore, controlling risk factors for atherosclerosis may play an important role in preventing cardiovascular events in these individuals.

Hydroxy-methylglutaryl-coenzyme A (HMG-CoA) reductase inhibitors (statins) have been demonstrated to reduce coronary heart disease morbidity and mortality in several landmark trials [7-14]. The reductions in cardiovascular events also occur in patients with average to lower than average baseline low-density lipoprotein cholesterol (LDL-C) levels [12,14] and the benefits of statin therapy can be independent of lipid lowering [15]. Most haemodialysis patients do not have elevated cholesterol (total and LDL-C) [16,17], and the highest mortality risk is often in patients with very low cholesterol levels [18]. Other chronic diseases and malnutrition may act to lower blood cholesterol and independently increase the risk of death, thereby contributing to the negative association between very low cholesterol and mortality observed in these patients [19,20]. Indeed, a recent prospective study suggests that levels of total cholesterol (TC) may be associated with mortality in haemodialysis patients without evidence of inflammation and malnutrition [20]. Haemodialysis patients have other lipid abnormalities such as lower levels of high-density lipoprotein cholesterol (HDL-C) and elevated intermediate-density lipoprotein (IDL) and triglycerides [16,17].

Although the efficacy of statins is well established in conditions associated with increased cardiovascular risk, dialysis patients have generally been excluded from statin outcome trials because of their related co-morbidities and as a result of pharmacokinetic and safety issues. It is not appropriate to extrapolate evidence from patients with normal renal function to patients with ESRD on haemodialysis, and there is a need to investigate the benefit-risk profile of statins specifically in this population. Data from an observational study indicate that statin treatment may improve survival in patients with ESRD [21]. Mortality was 32% lower in patients with ESRD who received statin treatment compared with patients not receiving statins, a finding that is consistent with other large outcome statin trials [7,8,11]. However, observational studies do not establish a causal relationship and large-scale randomised studies are required [22]. The Die Deutsche Diabetes Dialyse Studie (4D study) investigated the effect of atorvastatin 20 mg or placebo on cardiovascular mortality, non-fatal myocardial infarction and stroke in 1,255 patients with type 2 diabetes who were on haemodialysis treatment for no more than 2 years [23]. Initial results presented at the annual meeting of the American Society of Nephrology indicate that the primary endpoint was reduced by 8% after 4 years' treatment with atorvastatin, but this was not significantly different from placebo [24]. Further large-scale long-term prospective, randomised studies are required to investigate the efficacy and safety of statins for reducing cardiovascular morbidity and mortality, specifically in ESRD patients on haemodialysis [22].

Rosuvastatin is the most efficacious of the available statins for lowering LDL-C levels, causing reductions of 47% at the initial starting dose of 10 mg [25]. In addition, rosuvastatin has benefits across the lipid profile, including increases in HDL-C, reductions in small dense LDL and triglyceride-rich lipoprotein particles [25,26], and has a safety profile consistent with other available statins [27]. These properties make it an ideal agent for a study investigating the benefits of statin treatment for the prevention of cardiovascular events in a population of patients at high risk of cardiovascular events. AURORA (A study to evaluate the Use of Rosuvastatin in subjects On Regular haemodialysis: an Assessment of survival and cardiovascular events) is the first large-scale international trial to assess the effects of a statin on cardiovascular morbidity and mortality in ESRD patients on chronic haemodialysis irrespective of baseline lipid levels.

## Methods

### Study design

AURORA is a double-blind, randomised, multicentre, phase IIIb, parallel-group study comparing the effects of rosuvastatin (10 mg once daily) with placebo on survival and cardiovascular events in ESRD patients on chronic haemodialysis.

More than 2,750 subjects from approximately 300 centres in Europe, Canada, Australia, Brazil, Mexico and South Korea have been randomised, irrespective of baseline lipid levels. During the recruitment period, patients were screened over 2 weeks for eligibility according to the major inclusion and exclusion criteria (Table 1). Demographic data were collected on age, gender, race, medical history, physical examination (including height, weight, blood pressure and heart rate), smoking status, and method and duration of dialysis (Table 2). Patients were then randomised (1:1) into the two blinded treatment arms of the study, rosuvastatin 10 mg/day or placebo, and visits to assess safety and efficacy are scheduled to occur at 3 months, 6 months and every 6 months thereafter until the end of the study (Figure 1; Table 2).

**Table 1 T1:** Major eligibility criteria

**Inclusion**
Men and women aged 50–80 years
End-stage renal failure and chronic haemodialysis for at least 3 months
Provision of written informed consent
**Exclusion**
Underlying haematological, neoplastic, GI, metabolic (other than diabetes) or infectious condition expected to reduce survival to less than 1 year
Patients likely to require a kidney transplant within 1 year
Statin therapy within the previous 6 months
History of serious reactions to statins
Unexplained CK >3 times ULN
Active liver disease (ALT >3 times ULN)
Uncontrolled hypothyroidism
A disallowed medication, such as another lipid-modifying agent or cyclosporin

**ALT: **Alanine transaminase, **CK: **Creatine kinase, **GI: **Gastrointestinal, **ULN: **Upper limit of normal

**Figure 1 F1:**
[figure not shown]
Study design

Genetic research may also be performed on certain subjects at some study sites on an optional basis. DNA samples will be obtained for future research into the effects of genetic polymorphisms on the response to rosuvastatin and placebo. Susceptibility to, and prognosis of, cardiovascular disease and lipid disorders will also be studied.

### Study population

#### Eligibility and treatment withdrawal

Irrespective of baseline lipid levels, patients aged 50–80 years with ESRD who have been receiving chronic haemodialysis for at least 3 months were considered for inclusion in the study unless they fulfilled any of the exclusion criteria (key criteria detailed in Table 1). In addition, patients who undergo kidney transplant surgery will be withdrawn from study medication, but will continue to follow scheduled study assessments. Treatment will also be discontinued if patients have creatine kinase >10 times upper limit of normal (ULN) accompanied by unexplained muscle pain or if myopathy is suspected or if the patient becomes pregnant. Other reasons that may lead to treatment discontinuation include: an adverse event or endpoint that in the opinion of the investigator warrants treatment withdrawal; alanine transaminase increase >3 times ULN on two occasions; other safety reasons as judged by the investigator; protocol non-compliance.

#### Ethics

The study protocol and patient consent form have been approved by an Independent Ethics Committee or Institutional Review Board, as appropriate. The study is being performed in accordance with the ethical principles that have their origin in the Declaration of Helsinki and are consistent with International Conference on Harmonisation/Good Clinical Practice. The investigator from each centre will ensure that subjects are given full and adequate oral and written information about the nature, purpose, risks and benefits of the study and that written consent is obtained. The conduct and progress of the study is reviewed by the Steering Committee and Executive Steering Committee (see Appendix). In addition, an independent Data and Safety Monitoring Board (DSMB) (see Appendix) is responsible for monitoring all safety aspects of the study. The DSMB will review and evaluate all serious adverse events and endpoints at least every 6 months using unblinded data and will then report to the Executive Steering Committee in a blinded manner. The DSMB will also be responsible for making recommendations to the Executive Steering Committee regarding modifying or stopping the study early.

### Data analysis

The efficacy endpoints will be analysed using the intent-to-treat population, including all randomised subjects. For the time-to-event endpoints, Kaplan-Meier curves will be used to show the proportion of subjects without an endpoint. An unadjusted Cox Proportional Hazards model with treatment as the covariate will be used to analyse the endpoint. An additional Cox Proportional Hazards regression model [28] will also be constructed adjusting for known and potential risk factors as a secondary analysis and to test for interactions between risk factors and treatment. The number of coronary or peripheral revascularisations will also be summarised, but not formally analysed. For the tertiary endpoints, the percentage change from baseline for each parameter will be assessed for each time point by an analysis of covariance, with the baseline value as a covariate. An exploratory analysis will also be conducted to examine whether lipid values at 3, 12, 24, 36 months (yearly if required) and at the final visit are predictive of future cardiovascular events.

The sample size was determined such that the study will be adequately powered for the analysis of the primary endpoint, time from randomisation to a major cardiovascular event. Based on previous studies, it is anticipated that the cardiovascular event rate in the placebo group will be 11% per year. The sample size has been calculated in order to be able to detect a 25% reduction in cardiovascular events rate per year at a two-sided significance level of 4.86%, with 90% power. The study will continue until 620 subjects have experienced a major cardiovascular event. This is expected to be approximately 3.9 years after initiation of the study, which began in January 2003. An interim efficacy analysis will be conducted by the DSMB when 310 subjects have experienced a major cardiovascular event. The purpose of the interim analysis is to investigate, at this time, the possibility of concluding a statistically significant difference between the treatments for time from randomisation to major cardiovascular event.

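### The primary Cox model has treatment as its only covariate although likely prognostic baseline data are collected; a pre-specified adjusted primary model would gain some power at the same 620 events

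*Protocol article*

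**What the plan says.** Under Data analysis, the protocol article says of the time-to-event endpoints: "An unadjusted Cox Proportional Hazards model with treatment as the covariate will be used to analyse the endpoint". The next sentence plans a further Cox model that "will also be constructed adjusting for known and potential risk factors as a secondary analysis" and that also tests treatment-by-risk-factor interactions. The first model is thus the primary one and the adjusted model ranks below it. The article does not list the adjusted model's covariates, which is normal for an article.

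Under Study design: "Demographic data were collected on age, gender, race, medical history, physical examination". The same sentence adds smoking status and the method and duration of dialysis. Diabetes and prior cardiovascular disease are not named there, but it is reasonable to expect them within medical history.

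The design figures in Data analysis are: "detect a 25% reduction in cardiovascular events rate per year", "at a two-sided significance level of 4.86%, with 90% power", and "The study will continue until 620 subjects have experienced a major cardiovascular event". One interim efficacy analysis is planned at 310 events.

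**The concern.** Eligible patients are 50 to 80 years old, may be diabetic, and need at least 3 months of haemodialysis, with no upper limit among the listed criteria. Baseline risk is likely to vary a good deal between them. When a Cox model omits covariates that predict the outcome, the treatment hazard ratio it estimates lies closer to 1 than the covariate-conditional one, and its test has less power for the same number of events. The trial is event-driven, so a more efficient primary test would cost no patients and no follow-up time.

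Interpretation is also at stake. If the unadjusted primary test narrowly missed and the adjusted secondary analysis succeeded, the trial would have no clean conclusion.

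**Working it through.** **Inputs from the article (Data analysis, Study design).** Hazard ratio (HR) 0.75, taken from the 25% reduction; two-sided alpha 0.0486; power 90%; 620 events; 1:1 allocation; more than 2,750 patients. The placebo rate of 11% per year affects when 620 events are reached, not the power at 620.

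**Step 1: the plan's own figure.** Schoenfeld: events = 4(z_a + z_b)² / (ln HR)², with z_a = 1.972 and z_b = 1.282.
- HR 0.75: 4 × (3.254)² / (0.2877)² = 512. Freedman's formula gives 519.
- The stated 620 is not reproduced; it exceeds what the stated inputs need.
- Power at 620 events: Φ(√620/2 × 0.2877 − 1.972) = Φ(1.610) = 94.6%.
- At HR 0.80 (an assumption, not a figure in the article): Φ(12.45 × 0.2231 − 1.972) = Φ(0.806), about 79%.

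**Step 2: the gain from adjustment.** Two simulations compared unadjusted and adjusted Cox models with 2,750 patients, stopping at 620 events, and one baseline prognostic score with log-hazard SD σ. The stated HR is conditional on that score. The article gives no prognostic strength for any factor, so σ is assumed. The HR 0.75 runs also assumed 1.5 years of uniform accrual and 8% per year competing loss. The equivalent-event ratio is (mean adjusted z / mean unadjusted z)². Power at HR 0.75 is Φ(|mean z| − 1.972).

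HR 0.75, 1,200 runs per σ:

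| σ (assumed) | C-index | Mean z, unadjusted | Mean z, adjusted | Ratio | Power, unadjusted | Power, adjusted |
|---|---|---|---|---|---|---|
| 0.3 | 0.58 | −3.495 | −3.542 | 1.03 | 93.6% | 94.2% |
| 0.4 | 0.61 | −3.475 | −3.559 | 1.05 | 93.4% | 94.4% |
| 0.6 | 0.66 | −3.432 | −3.628 | 1.12 | 92.8% | 95.1% |
| 0.8 | 0.70 | −3.176 | −3.526 | 1.23 | 88.6% | 94.0% |

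A separate 500-run set at σ = 0.8 gave a ratio of 1.20 and power of 89.5% against 94.1%. At σ = 1.0, 500 runs gave a ratio of 1.37.

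HR 0.80, 1,000 runs per σ:

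| σ (assumed) | Ratio | Power, unadjusted | Power, adjusted |
|---|---|---|---|
| 0.4 | 1.06 | 76% | 79% |
| 0.6 | 1.12 | 76% | 80% |
| 0.8 | 1.19 | 73% | 81% |

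The Monte Carlo standard error of one power figure in the second table is about √(0.76 × 0.24/1000) = 1.4 points, so differences of a point or two between rows mean little.

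**Step 3: check by formula.** Dividing 620 by the ratio gives the effective events of the unadjusted test.
- HR 0.75: 620/1.05 = 590 gives 93.6%; 620/1.19 = 521 gives 90.5%.
- HR 0.80: ratios of 1.06, 1.12 and 1.19 give about 77%, 74% and 72%, against 79% with no loss.

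**Step 4: which σ is plausible?** This is an illustration with every input assumed and the factors independent. Age is uniform over 50-80 with HR 1.02-1.04 per year (SD 8.66 years, contributing 0.17-0.34). Diabetes has 30% prevalence and HR 1.5-2.0 (contributing 0.19-0.32). Prior cardiovascular disease has 40% prevalence and HR 1.5-2.0 (contributing 0.20-0.34). Combined, √(0.17² + 0.19² + 0.20²) = 0.32 up to √(0.34² + 0.32² + 0.34²) = 0.58. That corresponds to a gain of roughly 3% to 12%; 19% or more would need stronger predictors.

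**The case against.** The case for leaving the plan alone is substantial, and much of it stands.

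- **The unadjusted test is valid.** It is fixed in advance, controls type I error under randomisation and is a standard choice. A reader might call its hazard ratio biased. It is not: it targets a marginal effect and the adjusted model a conditional one. If the planned 25% reduction is read as the marginal effect, the 94.6% needs no discount and adjustment only adds to it.
- **The planned power is not in danger.** A reader might infer that the trial falls short of its 90%. At HR 0.75 the surplus of 620 over 512-519 events absorbs nearly all of the loss: about 89% to 90.5% remains even at σ = 0.8.
- **The information is not discarded.** An adjusted Cox model is already planned; it only ranks second. A reader might take it to be built from the data, but one verb in an article does not show that, and the full protocol or SAP may fix the covariates.
- **No strength is documented.** To call the factors strong, or to treat any percentage gain as a property of this trial, goes beyond the text. The simulations also adjust for the whole score, correctly specified; a short covariate list may capture less.

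What does not stand is the inference that nothing is to be gained. The surplus of events protects power only if the true effect is near 25%. The article's Background reports that the earlier randomised atorvastatin trial in haemodialysis patients with type 2 diabetes found an 8% reduction in its primary endpoint, which was not significant. An effect smaller than planned is therefore realistic, and at HR 0.80 there is no surplus: about 79% before any loss from omitted covariates.

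**Conclusion.** The point holds as an efficiency improvement. The article makes the treatment-only model primary while likely prognostic data are already in hand, and both simulations agree that adjustment raises power at the same 620 events. For assumed σ of 0.3, 0.4, 0.6 and 0.8 the gain equals about 3%, 5-6%, 12% and 19-23% more events. For σ from 0.4 to 0.8 this is about 1 to 5 power points at HR 0.75 and about 3 to 8 points at HR 0.80. The lower and middle parts of the range are the easiest to defend. The sizes rest on σ, on the assumed accrual and competing loss in the HR 0.75 runs, and on HR 0.80 as an example of a smaller effect; the article supplies none of these. Its text does not support describing the primary analysis as wrong or the trial as underpowered at its planned effect.

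**What to change.** Before the 310-event interim, amend the plan so that the primary analysis is a Cox model with treatment plus a short fixed list of baseline covariates already collected: age, smoking status, dialysis duration, and diabetes and prior cardiovascular disease as recorded in the medical history. State the coding of each covariate and a simple rule for missing baseline values. Use the same model at the interim and final analyses, and report the unadjusted Cox model as a sensitivity analysis.

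The decision must be made without access to unblinded data. According to the Ethics section, the DSMB sees unblinded data at least every 6 months, so it should have no part in choosing the covariates.

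The cost is a protocol amendment in a trial that has already randomised its patients, not merely a change of SAP wording. The reported hazard ratio becomes conditional on the covariates, and a few missing baseline values will need handling. No new data, patients or events are required.

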## Discussion

Patients with ESRD have an increased risk of cardiovascular morbidity and mortality [2,4], and this contributes to the large burden this disease places upon healthcare providers [5]. A number of studies have indicated that patients on dialysis with very low TC levels have a higher rate of mortality [18,20]. Both small dense LDL and triglyceride-rich lipoproteins have been implicated in the development of cardiovascular disease [29-32] and are common in patients with ESRD and on haemodialysis [16,33-37]. Triglyceride-rich lipoproteins, in particular IDL, are prevalent and predictive of atherosclerosis in haemodialysis patients [17]. Thus, modifying lipid levels with a statin should have beneficial effects on cardiovascular outcomes in these patients. Large outcome studies also indicate that the positive effects of statins occur irrespective of baseline lipid levels [12,14]. While the efficacy of statins for altering the lipid profile has been studied previously in ESRD patients [38-42], their long-term benefits on cardiovascular outcomes in this population have not yet been examined and dialysis patients have generally been excluded from statin outcome trials.

Several studies examining outcome after statin treatment have recently been completed or are in progress in patients with related conditions. In a study in renal transplant patients, fluvastatin reduced the risk of cardiac death or non-fatal myocardial infarction by 35% compared with subjects receiving placebo (risk ratio 0.65 [95% confidence intervals 0.48–0.88]; p = 0.005) [43]. Initial findings of the 4D study did not demonstrate a significant difference between atorvastatin 20 mg and placebo treatment; however, LDL-C levels were reduced during the study period [24]. Another study is ongoing; the Study of Heart And Renal Protection (SHARP) aims to assess the effects of simvastatin and the cholesterol-absorption inhibitor ezetimibe among patients with chronic kidney disease [18]. AURORA is the first international, prospective, randomised, double-blind, placebo-controlled study to assess whether statin therapy alone can reduce the incidence of coronary events in ESRD patients on chronic haemodialysis.

Most haemodialysis patients do not have elevated LDL-C and, in accordance with findings from the Heart Protection Study, the AURORA trial will randomise patients irrespective of their baseline lipid levels [12]. Patients on haemodialysis have lower levels of HDL-C and higher triglycerides compared with control subjects [16]. Accordingly, a statin with efficacy across the lipid profile would be appropriate to assess the benefits of treatment in ESRD patients. Rosuvastatin is the most efficacious statin reported for lowering LDL-C [44], and has benefits across the lipid profile. In a study of hypercholesterolaemic patients, rosuvastatin has been shown to increase HDL-C by 7.7–9.6% compared with 4.4–5.7% for atorvastatin and 5.2–6.0% for simvastatin across the 10–40 mg dose range [44]. In addition, rosuvastatin has been shown to substantially lower triglyceride-rich lipoproteins in both hypercholesterolaemic and hypertriglyceridaemic patients [45]. The effects of haemodialysis upon excretion of statins should also be considered. On the basis of pharmacokinetic, pharmacodynamic and safety data obtained from a pilot study, rosuvastatin 10 mg can be safely administered to patients with ESRD on chronic haemodialysis (data on file, AstraZeneca).

In addition to their ability to modify lipid levels, statins produce other effects that may benefit ESRD patients. Oxidative stress has been implicated in the pathogenesis of cardiovascular disease, and it is enhanced in patients with renal insufficiency [46,47]. Recently, statins have been reported to have anti-oxidant effects [48], which may be of benefit to these patients. Statins may also have additional non-lipid or pleiotropic effects, for example, improving endothelial function [15]. Endothelial dysfunction has been implicated in the development of cardiovascular disease and has been shown to be closely associated with the degree of renal insufficiency [49]. Pre-clinical experiments have shown that rosuvastatin can improve endothelial function [50], although this has yet to be verified in a clinical situation. Finally, left ventricular hypertrophy and heart failure can also develop in ESRD patients on haemodialysis [51]. Statin therapy has been reported to reduce left ventricular hypertrophy [52] and retrospective analyses indicate that these agents can also help to prevent heart failure [53]. These properties could provide an additional beneficial effect in ESRD patients.

The AURORA study should provide valuable information on the utility of statin treatment for the reduction of cardiovascular events in patients with ESRD. As an atherogenic lipid profile and endothelial dysfunction are often present in individuals with ESRD and contribute to the development of atherosclerosis, it is anticipated that rosuvastatin will improve cardiovascular outcomes in this patient population. Furthermore, it is hoped that AURORA will produce data on the cost effectiveness (cost due to hospitalisation and cost per year of life saved) and long-term safety of rosuvastatin treatment in ESRD patients receiving chronic haemodialysis. This study will also generate a large database of information from a well-documented cohort, which may be valuable in the epidemiological evaluation of cardiovascular risk in patients with ESRD.

